### Design

The project is a quasi-experimental design with two groups: 1) intervention groups with RN ACP facilitators, and 2) control groups without RN ACP facilitators. See Fig. 1. Research Flow Chart below.

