### Study setting and sample selection

Participants will be recruited from acute and community settings across LHD 1 and LHD 2, NSW, Australia. Research sites are listed below in Table 2.

**Table 2 Tab2:** Research sites

	Acute		Community	
	Intervention	Control	Intervention	Control
LHD 1	Geriatric Rehab Unit (LHD1**HIS**1)	Geriatric Rehab Unit (LHD1**HCS**3)	Public Community Health Centre (LHD1**CIS**5)	Public Community Health Centre (LHD1**CCS**7)
	Medical ward at Hospital (LHD1**HIS**2)	Medical ward at Hospital (LHD1**HCS**4)	Non-public Home and Community Care (LHD1**CIS**6)	Non-public Home and Community Care (LHD1**CCS**8)
LHD 2	Medical ward at Hospital (LHD2**HIS**9)	Medical ward at Hospital (LHD2**HCS**11)	Public Community Health Centre (LHD2**CIS**13)	Public Community Health Centre (LHD2**CCS**15)
	Medical ward at Hospital (LHD2**HIS**10)	Medical ward at Hospital (LHD2**HCS**12)	Non-public Home and Community Care Service (LHD2**CIS**14)	Non-public Home and Community Care Service (LHD2**CCS**16)

Note: Hospital Intervention Site (*HIS*), Hospital Control Site (*HCS*), Community Intervention Site (*CIS*), Community Control Site (*CCS*). One full-time RN for 2 wards in one hospital and one full-time RN for 2 community service providers at one setting are allocated in each LHD

The 16 research sites were pair-matched (eight intervention, eight control) and selection was based on admission rates, patient profile, number of deaths per month/year, average length of stay and number of referrals from/to hospital and community. To minimise potential contamination of intervention the sites chosen are geographically separated. Both public funded and non-public sites are involved in this research, to maximise the generalisability.

All newly admitted patients to a site listed as an ‘intervention site’ will be offered facilitated ACP conversations, and all other sites will continue to deliver usual care (control sites).

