#### Quantitative data analysis

Participant demographics and characteristics will be collected at each site and will be tabulated to show the distribution of participant characteristics between control and intervention sites (i.e. age, sex, primary reason for admission &/or chronic health condition). Continuous variables will be described by mean (standard deviation) if normally distributed and by median (interquartile range) otherwise. Categorical variables will be described by count (percentage). Group comparisons for continuous outcomes will be undertaken by either the Student t-test or Mann-Whitney U test. The Fisher’s Exact test will be used for categorical outcomes.

Baseline characteristics of study groups will be compared to assess similarity at study entry, thereby allowing for the identification of significant imbalances requiring adjustment during analysis. To account this and for clustering at the site level, multi-level regression models with mixed effects will be built to estimate interventional effect. For each model building process, variables found to be significantly associated with respective outcome measures in the univariable analysis at the 10% level will be retained in the final modelling.

As the primary predictor of interest, intervention effect will be forced into the multivariable modelling. Continuous outcome measures will be analysed using linear regression models. For binary outcome measures, analysis will be by binary logistic regression, while multinominal logistic regression will be used to analyse non-binary categorical measures. Model diagnostics will be conducted on all models.

All tests of significance will be set at 5%. Statistical analysis will be performed using Stata version 15.0 (StataCorp, College Station, TX, USA).

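### In this non-randomised 8 v 8 site comparison, adjustment variables are chosen only by significance tests, and outcome tests that ignore site stand beside a mixed model with nothing said about which decides

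*Protocol article*

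**What the plan says.** Under Design: "The project is a quasi-experimental design with two groups". Under Study setting and sample selection, sites were chosen and matched, not randomised: "The 16 research sites were pair-matched (eight intervention, eight control".

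The Quantitative data analysis section then gives two routes by which a covariate can reach the model:

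- Baseline characteristics are compared between the groups, "thereby allowing for the identification of significant imbalances requiring adjustment during analysis".
- In each model building process, "variables found to be significantly associated with respective outcome measures in the univariable analysis at the 10% level will be retained".

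Only one term is guaranteed a place: "intervention effect will be forced into the multivariable modelling".

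The section also gives two kinds of outcome comparison. Continuous outcomes get a Student t or Mann-Whitney test, and for the rest Fisher's "Exact test will be used for categorical outcomes". A later paragraph adds models: "To account this and for clustering at the site level, multi-level regression models with mixed effects will be built to estimate interventional effect". All tests are at 5%. No sentence ranks the simple tests against the models.

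**The concern.** Without randomisation, the credibility of the effect rests on adjusting for the right variables. A confounder distorts the estimate according to how strongly it relates to the outcome and how unequally it is spread across the arms. Whether either relation reaches significance in this sample is a different question, and with few events a real relation will often miss the threshold. Both routes to adjustment are significance rules, and the text does not say how they combine: a variable flagged as imbalanced may still fail the 10% screen for the final model.

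The second issue is independence. Whole sites sit in one arm, so patients at a site share its habits of raising and recording advance care planning. The t, Mann-Whitney and Fisher tests treat every patient as independent. The mixed model does not. Each outcome could thus carry two results at the 5% level, with no stated rule on which one supports the claim.

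**Working it through.** **Inputs.** From Sample size calculation: 288 patients, 25% non-response, 5% at baseline, a change of 10% (read as 5% to 15%), at least 10 admissions per week per site over six months. From Table 2: 16 sites. The documents give no intracluster correlation (ICC), no site variance and no confounder strength, so those are assumed and shown as ranges.

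**The plan's own figure.** For 5% v 15% at 80% power, the pooled two-proportion formula gives 111 per arm at one-sided 5%; 111/0.75 = 148, total 296. At two-sided 5% it gives 141 per arm, total 282 before non-response. The stated 288 lies within 3% of either. It is used here only as an input.

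**Two possible datasets.**
- Planned sample: 288 × 0.75 = 216, or 108 per arm. Events: 108 × 0.05 + 108 × 0.15 = 21.6, about 10%. Per site: 288/16 = 18, or about 14 after non-response.
- Full audit over six months: 10 × 26 = 260 per site; 260 × 16 = 4,160 records.

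**Step 1: the 10% screen.** Assume a binary confounder with 30% prevalence and an overall event rate of 10%. It is dropped when its univariable p-value is 0.10 or more.

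- OR 2: event rates 0.080 unexposed and 0.148 exposed. With 64.8 exposed and 151.2 unexposed, SE = √(0.148×0.852/64.8 + 0.080×0.920/151.2) = 0.049, so z = 0.068/0.049 = 1.38. Drop probability ≈ Φ(1.645 − 1.38) = 60%.
- OR 1.5: rates 0.088 and 0.127, SE 0.047, z = 0.82; Φ(1.645 − 0.82) ≈ 79%.
- Simulation with Fisher's test as the screen: about 58% at OR 2 and about 80% at OR 1.5.
- At 4,160 records z grows by √(4160/216) = 4.39. OR 1.5: z = 3.58, drop probability Φ(−1.93) ≈ 3%. OR 2: z = 6.06, about 0%. With rarer events (4% in the unexposed), the OR 1.5 figure rises to about 17%.

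**Step 2: the bias this leaves.** Simulation with 108 per arm, no intervention effect, 5% risk in the unexposed, and confounder prevalence 30% v 70% between arms. If the 10% screen governs, the median intervention OR is 1.13, 1.14 and 1.06 for confounder ORs of 1.5, 2 and 3. With the confounder forced in it is 1.00 to 1.01. The type I error of the screened model stays at 3% to 4%. An imbalance this large would be seen at baseline: 0.40/√(2×0.3×0.7/108) = 0.40/0.062 = 6.4 standard errors. So this bias arises only if the outcome screen overrides the baseline flag, which the text leaves open.

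**Step 3: outcome tests that ignore site.** Take 5% prevalence and no effect. Logit-normal site SDs of 0.3, 0.5 and 0.7 correspond to ICCs of about 0.004, 0.012 and 0.027. Design effect = 1 + (m − 1) × ICC; actual type I error of a nominal 5% test ≈ 2[1 − Φ(1.96/√design effect)].

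| ICC | Design effect, m = 260 | Approximate type I error |
|---|---|---|
| 0.004 | 1 + 259×0.004 = 2.04 | 17% |
| 0.012 | 1 + 259×0.012 = 4.11 | 33% |
| 0.027 | 1 + 259×0.027 = 7.99 | 49% |

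Simulation of Fisher's test on 8 v 8 sites of 260 gives the same range, about 17% to 50%. A site-level t-test (14 df) on the same data holds 4% to 5%.

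At 14 to 18 per site the design effect is at most 1 + 17×0.027 = 1.46, and Fisher's test is conservative with about 7 events per arm (144 × 0.05 = 7.2). Simulated type I error is about 3% to 8%. Larger ICCs would raise it: 10% at ICC 0.05 and 17% at 0.10, with 18 per site.

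**The case against.** Several stronger readings are tempting, and the document does not support them.

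- *Confounders enter only at univariable p < 0.10.* The baseline comparison is a second route, so a strongly imbalanced variable is at least flagged. That route is also a significance rule, and its standing in the final model is unstated, so the criticism survives as one of significance-driven choice.
- *The planned p-values for the intervention effect are wrong.* That effect is to come from multi-level models that allow for site, and a natural reading makes those models the main analysis. The inflation applies to the simple tests. They are, however, set for outcomes rather than baseline characteristics, under a sentence that fixes all tests at 5%, and nothing calls them preliminary.
- *Both problems are large at once.* They are not. Confounders are dropped mainly in the sample of about 216; false positives arise mainly on the full audit. Each dataset has chiefly one of the two problems.
- *Intervals after selection are too narrow.* This was not shown; in the simulation the screened model kept its type I error.
- *Ignoring the pair-matching is an error.* With a site random effect in the model, leaving out the pairs mainly costs precision, and a pair term may properly be left to an analysis plan that is not shown.

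The general defence, that detail belongs in the analysis plan, does not reach the two rules criticised here, because the article states them itself.

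**Conclusion.** The point holds in limited form. Choosing covariates by significance, with only the intervention forced in, is a poor rule for a non-randomised comparison of 16 sites. At the planned sample it would miss a moderate confounder more often than not (about 58% at OR 2, about 80% at OR 1.5), assuming 30% prevalence and about 22 events. The bias per factor is modest (intervention OR about 1.06 to 1.14 under no effect, with strong imbalance and the 10% screen governing). On about 4,160 audit records the rule would seldom matter.

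The outcome tests without allowance for site are harmful chiefly if the full audit is analysed: about 17% to 50% false positives for assumed logit site SDs of 0.3 to 0.7, against about 3% to 8% at 14 to 18 per site. The defect in the text is that these tests and the mixed model stand side by side with no statement of which one decides. This should be changed before analysis; it does not invalidate the planned mixed model.

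**What to change.** 1. Replace both significance-based rules with a prespecified covariate set forced into every model: age, sex, chronic condition, and LHD by setting (the four strata of Table 2). The patient variables are already to be collected. Tabulate baseline characteristics without using tests to choose covariates.
2. State that the mixed model with a site effect is the sole basis for inference on the intervention effect, and add a site-level analysis as a small-sample check, since there are only 16 clusters.
3. Make the t, Mann-Whitney and Fisher comparisons of outcomes descriptive only, or delete them.

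A matched-pair term or a permutation test is optional.

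The cost is wording and a few degrees of freedom. With intervention (1), age (1), sex (1), strata (3) and a two-level condition grouping (1), the model has 7 terms. Against about 22 events that is about 3 events per term, so in the smaller dataset condition should be grouped coarsely. On the audit, 5% of 4,160 is already 208 events and the cost is slight.

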## Methods/design

### Aims

The primary aim: To test the feasibility and effectiveness of normalisation of ACP for people with chronic diseases in acute and community settings.

The secondary aims are:To identify the characteristics of the most effective setting and demographics for ACP implementation.To investigate the nature and extent to which planning for future health care wishes are initiated, discussed and documented among people with chronic diseases, their family members, and RN ACP facilitators.To identify the effect of ACP on patient/SDM satisfaction with their healthcare experience.To identify factors that influence the implementation of ACP in hospital and community health settings.To assess and estimate the financial impact of normalisation of ACP on our health care system.

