### Sample size calculation

Power calculations were conducted to determine the sample size required to detect a change of at least 10% in the primary outcome; that being the proportion of completed NSW ACDs. Change was defined as the difference between the proportion at baseline, assumed to be 5% and at follow-up. Setting alpha at 5%, power at 80% and assuming a non-response rate of 25%, a sample size of 288 is needed (144 in intervention sites and 144 in control sites). Given an average admittance rate of at least 10 per week per site and over a six-month period, there is almost complete surety that the study will not be under-powered.

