### Data collection

#### Audit of ACP related practice

Data on the prevalence of ACP and ACDs will be collected through an audit of the medical records of patients admitted to the 16 research sites within the following time frames:The two month period before the introduction of the intervention period,The six month period of the intervention

The audit will initially check for the presence or absence of evidence of ACP only. Then the individuals whose medical records contain evidence of ACP will be invited to consent to access the content of ACDs (or documentation detailing personal values or specific wishes relating to medical care &/or organ donation). The audit involves the following steps.Medical records from all individuals admitted to a research site at the given times will be requested from relevant medical records departments. Records will be audited for the presence or absence of ACP only.Medical Record Numbers (MRN) of those containing evidence of ACP will be recorded. They will then be posted a letter of invitation and consent form with a pre-paid, self-addressed envelope.The individuals will return the consent form directly to the Research team. Where a completed consent form is returned, the individuals’ medical records will be re-accessed to collect information to assess the quality and completeness of any ACP or ACD, and whether there is concordance of care with the individuals expressed wishes, values and beliefs.

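### Any secondary outcome recorded in ordered categories would be analysed without its order, because the plan assigns multinomial regression and Fisher's exact test with no ordinal exception

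*Protocol article*

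**What the plan says.** The section on quantitative data analysis allocates models by data type: linear regression for continuous outcomes, binary logistic regression for binary ones, and for the rest "multinominal logistic regression will be used to analyse non-binary categorical measures". For simple group comparisons, "The Fisher’s Exact test will be used for categorical outcomes". The only rank method named is tied to another data type: "Group comparisons for continuous outcomes will be undertaken by either the Student t-test or Mann-Whitney U test". The regression models are multilevel, to allow for clustering by site, and diagnostics are promised for all of them.

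Two secondary measures could be graded. One secondary aim is "To identify the effect of ACP on patient/SDM satisfaction with their healthcare experience", and Table 4 shows surveys of patients and SDMs at both intervention and control sites. The audit section re-opens the records of consenting people "to collect information to assess the quality and completeness of any ACP or ACD". No instrument, scale or number of levels is given for either.

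The sample size section defines "the primary outcome; that being the proportion of completed NSW ACDs", which is binary and goes to binary logistic regression.

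**The concern.** The rule covers every categorical measure with more than two levels and has no branch for ordered ones. A detailed analysis plan that followed it would have to treat, say, a five-point satisfaction item as five unrelated labels. This is a stated choice of method, not a detail left for later.

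If an outcome is ordered, two things are lost. First, the intervention effect is spread over k-1 degrees of freedom, so the test asks whether the category shares differ in any way, not whether responses move up or down. Second, the result is k-1 odds ratios with no single summary. Fitting several category-specific effects with a site effect, over 16 sites and with possibly sparse cells, is also harder than fitting one common odds ratio.

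**Working it through.** **The plan's own figure.** The article states no power for any non-binary categorical outcome. Its only sample size figure is 288 (144 per group) for the binary primary outcome, from 5% at baseline, a 10-point change, 80% power, 5% alpha and 25% non-response. With a one-sided alpha and the unpooled formula:

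n = (1.645 + 0.842)² × (0.05×0.95 + 0.15×0.85) / 0.10² = 6.183 × 0.175 / 0.01 = 108.2 per group, and 108.2 / 0.75 = 144.3.

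A two-sided pooled calculation gives 141 before non-response and 188 after it. Sidedness is a separate matter and does not bear on this point. What is used here is the number of responders the plan implies: 144 × 0.75 = 108 per arm.

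**Assumptions, none of them from the documents.** 3 to 5 ordered levels; a common odds ratio across cut-points; two-sided 5%; 108 per arm borrowed from the primary outcome; site clustering ignored.

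**Step 1: cost of the extra degrees of freedom.** A 1-df test with 80% power has non-centrality (1.960 + 0.842)² = 7.85. The same non-centrality on more degrees of freedom gives:

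| Levels k | df = k-1 | Power |
|---|---|---|
| 2 | 1 | 80.0% |
| 3 | 2 | 70.9% |
| 4 | 3 | 64.5% |
| 5 | 4 | 59.5% |

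**Step 2: an odds ratio of 2 at 108 per arm, analytically.** Under proportional odds, the information on the log odds ratio is V = (N/12)(1 − Σp̄³), where N = 216 and p̄ is the mean of the two arms' category probabilities. The non-centrality is (ln 2)² × V = 0.4805 × V. With a control arm spread evenly over five levels, Σp̄³ = 0.045, so V = 18 × 0.955 = 17.19 and the non-centrality is 8.26. Ordinal power is Φ(√8.26 − 1.96) = Φ(0.91) = 82%. The multinomial likelihood-ratio test has non-centrality 8.11 on 4 df, which gives 61%.

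**Step 3: simulation** (4,000 runs, odds ratio 2, 108 per arm). Pearson's chi-square stands in for Fisher's exact test, and the Wilcoxon test for the proportional-odds score test.

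| Control distribution | Multinomial LR | Pearson/Fisher | Ordinal (rank) | LR loss, points |
|---|---|---|---|---|
| 3 levels, even | 0.687 | 0.683 | 0.772 | 8.5 |
| 3 levels, skewed | 0.566 | 0.558 | 0.659 | 9.3 |
| 4 levels, even | 0.661 | 0.658 | 0.808 | 14.7 |
| 5 levels, even | 0.611 | 0.602 | 0.810 | 19.9 |
| 5 levels, skewed | 0.598 | 0.581 | 0.793 | 19.5 |

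The formula and the simulation agree at roughly 10 points for three levels and 20 for five.

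**Step 4: sensitivity to the assumptions.**
- More levels: with seven even levels, a test with 80% ordinal power has about 51% as a multinomial test, a loss of 29 points.
- Smaller samples: at 54 per arm the loss is about 7 to 23 points across the cases run and the two unordered tests.
- Non-monotone effect: with five levels moving from (0.2, 0.2, 0.2, 0.2, 0.2) to (0.3, 0.15, 0.1, 0.15, 0.3), the multinomial test has power 0.68 and the rank test 0.05. The ranking reverses.

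**The case against.** The strongest objection is that the premise is not in the document. Nothing says that satisfaction or document quality is recorded in ordered categories. A summed satisfaction score would go to linear regression with a t-test or Mann-Whitney test, and yes/no items to binary logistic regression; the rule would touch neither. Much of the audit is counts or presence and absence. This stands, and it makes the point conditional. A reader might infer that these two outcomes are graded and that the trial will therefore lose 10 to 20 points of power. The article does not support that.

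The magnitude is also conditional. The 108 per arm belongs to the primary outcome. The survey is voluntary and its number of respondents is not given. Document quality is assessed only in people whose records show ACP and who return a posted consent form. Clustering was not modelled, so the gap between the mixed models that would actually be fitted is not known. All of this stands.

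A reader might also infer that Fisher's test decides what enters the final model. The article does not name it as the test for the 10% univariable screen, and the intervention term is forced into the model in any case. Only its use as a group comparison is at issue.

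Finally, multinomial regression is valid for ordered data and avoids the proportional-odds assumption, and the discussion claims good power only for the primary outcome and the cost-effectiveness calculations. This also stands: nothing is biased and no stated power figure is contradicted.

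The argument that an article leaves such matters to the analysis plan carries less weight. The scales may fairly be left to it, but the model for all non-binary categorical measures is fixed here.

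**Conclusion.** The point holds in conditional form and for secondary outcomes only. If an outcome is recorded in three or more ordered levels, the stated methods discard the order and give k-1 odds ratios where one would serve. The cost is roughly 10 points of power with three levels and 20 with five, under a common odds ratio, about 108 responders per arm and independent observations. It would be larger with more levels and would reverse for a non-monotone effect. For document quality the sample is unknown and likely smaller than 108 per arm. If no secondary outcome turns out to be ordinal, the rule does no harm. The fault is inefficiency and a less direct answer, not invalidity.

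**What to change.** In the section on quantitative data analysis:

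- State that ordered categorical outcomes are analysed by mixed-effects ordinal (proportional-odds) logistic regression with a site random effect, reporting one common odds ratio.
- For those outcomes, replace Fisher's exact test with a rank or trend test in the group comparison.
- Keep multinomial regression for truly unordered outcomes, and as a sensitivity analysis where the proportional-odds check fails. This also covers a non-monotone effect.

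The cost is a few sentences of wording and no new data. The downside is the proportional-odds assumption, which the model diagnostics already planned can check.

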**Methods:**

The aim of this study is to investigate the effects of normalising ACP in acute and community settings with the use of specially trained normalisation agents. This is a quasi-experimental study, involving 16 sites (8 intervention and 8 control) in two health districts in Australia. A minimum of total 288 participants will be recruited (144 intervention, 144 control). We will train four registered nurses as normalisation agents in the intervention sites, who will promote and facilitate ACP discussions with adult patients with chronic conditions in hospital and community settings. An audit of the prevalence of ACP and Advanced Care Directives (ACDs) will be conducted before and after the 6-month intervention period at the 16 sites to assess the effects of the ACP service delivered by these agents. We will also collect interview and survey data from patients and families who participate, and healthcare professionals who are involved in this service to capture their experiences with ACP.

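### With 8 v 8 sites and no finite-cluster method named, an uncorrected test of a post-period contrast on the full audit runs at about 6-9% rather than the stated 5%

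*Protocol article*

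**What the plan says.** The abstract gives "16 sites (8 intervention and 8 control"), and Study setting and sample selection adds "The 16 research sites were pair-matched (eight intervention, eight control"). Whole sites either have the ACP service or do not, so treatment varies only between sites.

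Under Quantitative data analysis, "multi-level regression models with mixed effects will be built to estimate interventional effect", allowing for baseline imbalance and for site clustering. Binary outcomes are analysed by logistic regression, and "All tests of significance will be set at 5"%. That section names no test statistic, reference distribution, degrees of freedom or small-sample correction.

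Under Data collection, the audit takes the records of everyone admitted to the 16 sites, in a two-month window before the intervention and during the six intervention months. Sample size calculation gives the volume: "Given an average admittance rate of at least 10 per week per site and over a six-month period". It also defines the effect: "Change was defined as the difference between the proportion at baseline, assumed to be 5% and at follow-up".

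**The concern.** With 16 sites, a between-site contrast carries about 14 degrees of freedom however many records each site contributes, and fewer if the matched pairs are modelled. A default mixed logistic fit estimates the site variance by maximum likelihood, which is biased downward with 16 units, and refers the result to a normal or chi-squared distribution that ignores the uncertainty in that variance. The more records per site, the more the standard error rests on the poorly estimated site variance.

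At stake is the error control of the primary comparison. A p-value a little under 0.05 could be reported as an effect of the service without the protection that the 5% level implies, and nominal 95% intervals would cover less than 95%.

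**Working it through.** **The plan's own figure.** The 288 is (approximately) a calculation for independent patients. For 5% v 15%, one-sided 5% and 80% power, unpooled:

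n = (1.645 + 0.842)² × (0.05×0.95 + 0.15×0.85) / 0.10² = 108.2 per group, and 108.2 / 0.75 = 144.3, close to 144.

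A two-sided pooled formula without the non-response allowance gives 141. Neither version contains a site variance, so none can be recovered from the 288 and a range has to be assumed.

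**Inputs.**
- Sites: 8 v 8 (abstract; Study setting and sample selection).
- Audited records per site: 10 per week × 26 weeks = 260 in the intervention period, and about 87 in the two-month baseline window.
- ACD rate: 5% (Sample size calculation).
- If only the 288 are analysed: 288 / 16 = 18 per site.
- Assumed: latent-scale ICC 0.01-0.20. SD = √[ICC/(1−ICC) × π²/3] gives 0.18-0.91.

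**Why records per site matter.** The sampling variance of a site's log-odds is about 1/(n×0.05×0.95): 0.081 at n = 260 and 1.17 at n = 18. The site variance at SD 0.4 is 0.16. It is the larger component at 260 records and the smaller one at 18.

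**Large-site approximation.** If site log-odds are treated as observed normal values, the maximum-likelihood variance divides by 16 where the unbiased one divides by 14.
- Wald z rejects when |t₁₄| > 1.960 × √(14/16) = 1.833, which has probability 8.8%.
- The likelihood-ratio test rejects when 16·ln(1 + t²/14) > 3.841, that is |t₁₄| > 1.949: 7.2%.
- Wald referred to t with 14 df rejects when |t₁₄| > 2.145 × √(14/16) = 2.006: 6.5%.

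**Simulation.** Null true, random-intercept logistic model fitted by maximum likelihood (15-point adaptive quadrature), site as the only and correct level. There were 4,000-10,000 trials per post-period setting and 2,000 for the pre-post setting; Monte Carlo SE is about 0.3-0.5 points. Figures are % rejecting at nominal 5%.

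| Setting (5% rate) | Wald z | LR | Wald, t(14) | Site-level t-test |
|---|---|---|---|---|
| Post-period, 260/site, ICC 0.01 (SD 0.18) | 6.8 | 6.2 | 4.9 | 5.0 |
| ICC 0.02 (SD 0.26) | 7.4 | 6.2 | 5.2 | 4.5 |
| ICC 0.03 (SD 0.32) | 8.2 | 6.8 | 5.7 | 4.6 |
| ICC 0.05 (SD 0.42), two runs | 8.4-9.1 | 6.9-7.6 | 6.2-6.6 | 4.8-4.9 |
| ICC 0.10 (SD 0.60), two runs | 8.4-8.6 | 7.1-7.2 | 6.3-6.5 | 4.9-5.1 |
| ICC 0.20 (SD 0.91) | 9.0 | 7.4 | 6.7 | 5.2 |
| Post-period, 18/site, ICC 0.01-0.10 | 3.7-4.9 | 5.5-6.6 | 1.5-2.6 | 5.3-5.9 |
| Pre-post interaction, 87 + 260/site, ICC 0.05, no drift | 5.0 | 5.1 | 2.8 | 3.9 |

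At a 10% rate and ICC 0.05 with 260 per site, Wald z gives 8.6% and LR 7.1%. Repeat post-period runs at site SD 0.2, 0.4 and 0.6 gave Wald z 7.0%, 8.4% and 8.2%, with 4.8-6.3% against t(14) and 4.0-5.6% for a site-level t-test.

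**Pre-post contrast when sites drift.** Site SD 0.4, 87 + 260 per site, 1,500 trials per setting, with a site-by-period random effect included in the fit. Wald z rejects 7.7% at drift SD 0.3 and 8.9% at 0.4. A t-test on the 16 site-level changes gives 4.8% and 5.2%. Leaving that random effect out gives 12.4% and 21.2%, which is a separate question of which level is modelled.

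**The case against.** The article never says that a Wald z test will be used. The 5% sentence fixes only the level, and test statistics and degrees of freedom are often left to a statistical analysis plan that is not shown here. A reader might infer that the protocol commits to a large-sample test, or that its primary test runs at nearly double the stated level. The documents support neither. The first is not stated. The second would need a Wald z test, a post-period contrast, the full audit and moderate site variation, all together.

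The effect is also defined from baseline to follow-up, and a pre-post interaction without differential drift holds 5%. That limits the point, but does not remove it. Quantitative data analysis names no period term or interaction, only an intervention effect forced into the model, so a post-period contrast remains a natural reading. The assumption of no drift is nowhere stated.

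Finally, this is a non-randomised comparison, and the mixed model is the means of adjusting for baseline imbalance. Replacing it with an unadjusted site-level test would lose that adjustment, and a permutation test would have no randomisation behind it. This objection stands in full, and the fix keeps the model.

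**Conclusion.** The point holds as a conditional one. The article fixes the model class, the number of sites, the 5% level and an audit of all admissions, and that combination does not by itself deliver 5%. For a post-period between-site contrast with about 260 records per site and a 5% rate, the false-positive rate is about 7-9% with an uncorrected Wald z test and about 6-8% with a likelihood-ratio test. Uncorrected Wald 95% intervals then cover about 91-93% under the null.

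These figures rest on assumed site SDs of roughly 0.2-0.9 on the logit scale. The excess is at the low end when sites are alike. It disappears for the Wald test at 18 records per site, and for a pre-post contrast without differential drift. It returns for a pre-post contrast when sites drift differently. The defect is moderate and cheap to close.

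**What to change.** Add to Quantitative data analysis that the primary p-value and confidence interval for audit outcomes use between-site degrees of freedom, by one of two routes:

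1. Refer the covariate-adjusted mixed-model effect to a t distribution with 14 df, or fewer if site-level covariates or the matched pairs are modelled. In the post-period simulations this gave about 5-6.7%.
2. Report a t-based analysis of site-level proportions, or of site-level pre-post changes, alongside the mixed model. In the post-period simulations this gave about 4-5.6%.

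In either case keep the mixed model for baseline adjustment, and state whether the effect is a post-period or a pre-post contrast.

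The cost is wording and slightly wider intervals. The critical value is 2.14 at 14 df (2.145/1.960 = 1.09, about 9% wider) or 2.36 at 7 df if pairs are used (2.365/1.960 = 1.21, about 21% wider). Where there was no inflation to remove, route 1 is conservative: 1.5-2.6% at 18 records per site and 2.8% for a pre-post contrast without drift. Route 2 stays nearer to 5% there (5.3-5.9% and 3.9%).
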